## Abstract

**Background:**

Preterm birth is the leading cause of perinatal morbidity and mortality. Risk factors for preterm birth include a personal or familial history of preterm delivery, ethnicity and low socioeconomic status yet the ability to predict preterm delivery before the onset of preterm labour evades clinical practice. Evidence suggests that genetics may play a role in the multi-factorial pathophysiology of preterm birth. The All Our Babies Study is an on-going community based longitudinal cohort study that was designed to establish a cohort of women to investigate how a women's genetics and environment contribute to the pathophysiology of preterm birth. Specifically this study will examine the predictive potential of maternal leukocytes for predicting preterm birth in non-labouring women through the examination of gene expression profiles and gene-environment interactions.

**Methods/Design:**

Collaborations have been established between clinical lab services, the provincial health service provider and researchers to create an interdisciplinary study design for the All Our Babies Study. A birth cohort of 2000 women has been established to address this research question. Women provide informed consent for blood sample collection, linkage to medical records and complete questionnaires related to prenatal health, service utilization, social support, emotional and physical health, demographics, and breast and infant feeding. Maternal blood samples are collected in PAXgene™ RNA tubes between 18-22 and 28-32 weeks gestation for transcriptomic analyses.

**Discussion:**

The All Our Babies Study is an example of how investment in clinical-academic-community partnerships can improve research efficiency and accelerate the recruitment and data collection phases of a study. Establishing these partnerships during the study design phase and maintaining these relationships through the duration of the study provides the unique opportunity to investigate the multi-causal factors of preterm birth. The overall All Our Babies Study results can potentially lead to healthier pregnancies, mothers, infants and children.

## Background

Preterm birth remains poorly understood in modern society despite accounting for 75% of perinatal mortality [1,2]. Moreover, the rate of preterm birth, that is birth before 37 completed weeks of gestation, has been on the rise for the past 3 decades in many developed countries including Canada, the USA and European nations where current rates range between 5-12% [3]. Infants born preterm are at increased risks for neonatal complications and associated long-term morbidity [4] such as developmental delays, hearing and vision impairments, respiratory distress syndrome, cerebral palsy and retinopathy of prematurity, prolonging the financial, emotional and stress-related costs of prematurity well beyond the care received within neonatal intensive care units. The risk for adverse neonatal outcomes is inversely related to gestational age at birth with the highest morbidity among those infants delivered prior to 28 completed weeks of pregnancy (early preterm) [5] despite technological advances and improved medical treatments having greatly increased the survival of these infants [6,7]. The rate of late preterm births (34-36 weeks gestation) has also continued to climb and accounts for 75% of all preterm infants [8]. Recent studies have shown that these late preterm infants are at higher risk for adverse acute and long-term outcomes when compared to term infants [9].

The pathophysiology of preterm birth is complex due to multi-factorial causes and its heterogeneous nature. Preterm birth is often categorized as (1) iatrogenic when delivery is a consequence of medical intervention (30-35%); (2) spontaneous when it occurs after spontaneous labour with intact membranes (40-45%); or (3) the result of preterm premature rupture of the membranes (PPROM) (25-30%) [3]. While gestational diabetes, preeclampsia and intrauterine growth restriction have all been associated with iatrogenic preterm birth, the underlying causes of spontaneous preterm birth are less clear. Reported risk factors are widespread and diverse, supporting the hypothesis of gene-gene and gene-environment interactions in the pathophysiology of spontaneous preterm birth. Highly associated risk factors include a previous preterm birth or a relative with preterm birth [10] or a black racial background [11], suggesting genetic causes. Other demographic factors such as low socioeconomic status [12] and maternal stress [13] have shown an association, indicating that the environment contributes to the etiology of spontaneous preterm birth.

Evidence for a causal role of infection and inflammation in preterm birth has been reviewed in detail [14]. Both interleukin (IL)-1β and tumor necrosis factor (TNF)α are cytokines produced by the intrauterine tissues in response to bacterial infections [15,16] which stimulate prostaglandin synthesis [17] and increase uterine contractility. Several groups have investigated the relationship between a single nucleotide polymorphism (SNP) located in the promoter of the TNFα gene (G-308>A) (referred to as the TNF-2 allele) and preterm birth, but inconsistent results have been reported [18-21]. A recent meta-analysis of seven studies [22] found no association between preterm parturition and the TNF-2 allele. Similarly, studies examining polymorphisms in IL-1β and IL-6 as well as other variants have also produced inconsistent results [19,23,24].

These inconsistencies may be the result of gene-environment interactions impacting the effects of potential genetic predispositions to preterm birth. For example, Macones *et al*. reported an increased risk of preterm delivery being associated with both the TNF-2 allele and the presence of bacterial vaginosis, but not with either factor alone [25] suggesting a synergistic interaction. These findings highlight the complexity of understanding preterm birth and the need for an interdisciplinary approach, a strategy embraced by the Preterm Birth International Collaborative (PREBIC) in recently published guidelines for preterm birth research [26].

Prediction of risk for preterm birth is critical to successful clinical management. Understanding risk and protective factors is best accomplished through the development of a pregnancy cohort where asymptomatic women can be prospectively recruited and followed over time. Despite our growing awareness that infection, inflammation, stress and other risk factors contribute to the pathophysiology of preterm birth, predicting which women will deliver preterm remains an ongoing challenge. Many biomarkers for preterm birth have been suggested and explored such as fetal fibronectin [27,28], maternal corticotropin releasing hormone (CRH) [29], and cervical length [30] however all have had limitations such as low positive predictive values, low sensitivity or poor specificity [31] in addition to high inter-individual variability, which limit their translation into clinical settings. Bocking *et al*. have shown that white blood cell (leukocyte) counts [32] or the presence of infection [33] at 22-27 weeks gestation is an accurate predictor of preterm birth before 28 weeks gestation. These researchers have also shown CRH or combination of CRH and maternal age to be predictive for mid to late preterm deliveries respectively. Recent multiple-marker tests for risk of preterm birth show promise but continue to have limited predictive power for non-labouring women [34].

A clinical screen for risk of preterm delivery before women have signs or symptoms of preterm labour is needed. The evidence also suggests that an interdisciplinary approach is required to understand preterm birth pathophysiology. The purpose of this paper is to describe the methodology for community based recruitment of a pregnancy cohort, The All Our Babies Cohort Study, to examine genetic, environmental and pathophysiologic contributions to preterm birth.

## Methods/Design

### Objectives

The aims of the All Our Babies Cohort Study are

a) To investigate genetic components of preterm birth through comparisons of transcriptomic patterns at 18-22 weeks and 28-32 weeks of pregnancy between spontaneous preterm birth cases and term delivering controls,

b) To examine the association between environmental factors and preterm birth, including access to routine prenatal care and health services, maternal mental and psychosocial health during pregnancy, and;

c) To examine the relative impact of genes and environment on the risk of preterm birth by exploring the interactions between medical history, gene expression patterns and environmental variables.

### Study Design

The All Our Babies Cohort Study is a community-based prospective pregnancy cohort study to determine the environmental and genetic risks for preterm birth.

### Study Population

The study population is drawn from all women who receive prenatal viral serology testing in Calgary, Alberta, Canada. Participants reside within the Calgary city limits and surrounding rural communities. Women are recruited through a partnership with the clinical laboratory service in Calgary.

### Inclusion Criteria

Inclusion criteria for the All Our Babies Cohort Study are designed to ensure women most at risk of preterm birth are captured in the cohort.

1. Women <17 weeks 6 days gestation at time of recruitment

2. Women receiving prenatal care in Calgary

3. Women able to understand written and spoken English

4. Age 18 years or older at time of enrollment

5. One of the following pregnancy histories:

a. Nulliparous or primiparous OR

b. A personal or familial history of preterm birth

6. Singleton pregnancy

### Exclusion Criteria

1. Planned to move outside of the greater Calgary area during their pregnancy

2. Known to be carrying multiples at the time of enrollment

3. Had any of the following pre-existing medical conditions

a. Type I or Type II diabetes

b. High blood pressure or hypertension

c. Autoimmune/immune disorders: lupus, rheumatoid arthritis, Sjogren's syndrome

d. Kidney disease, chronic renal disease, nephritis, nephropathy, dialysis

e. A heart problem that was repaired by surgery

f. Chronic infection: hepatitis, HIV

### Recruitment Strategies

Prenatal clinical practice guidelines prompt evaluation of viral serology by public health laboratories. The sole provider of phlebotomy for this service in the Calgary region is Calgary Laboratory Service. Women with laboratory orders for prenatal viral serology tests are contacted by telephone by the clinical laboratory to ask for permission to release their contact information to the research staff. Women that consent to the release of their information are subsequently contacted by telephone to determine eligibility, inform them about the study and invite them to participate. Women who provide verbal consent to participate are enrolled in the study and are mailed a record of the consent form for their records. Written consent for blood collections and associated genetic analyses is obtained at the time of the first blood collection and prior to the blood draw.

### Questionnaire Data Collection

Questionnaires were developed to address the objectives of the All Our Babies Cohort Study and included input from academics, stakeholders and decision makers. These questionnaires (available on request) assess demographics, pregnancy history, service utilization, nutrition and exercise practices, mental health, social support, lifestyle and life history, and breastfeeding experiences through questions designed for this study as well as the following validated instruments: Edinburgh Postnatal Depression Scale [35], Spielberger State Anxiety Scale [36], MOS Social Support Scale [37], Perceived Stress Scale [38], T-ACE Screen for alcohol consumption risk [39], Parenting Morale Index [40], the Parental Expectations Scale for parenting self-efficacy [41], and the MCH Feeding Scale (personal communication, [name], Feeding Problem Questionnaire 2003). The questionnaires were pilot tested prior to study commencement and revised for unclear wording. The questionnaires were designed using the Cardiff Teleform software suite (Cardiff Teleform, Version 10.1, 2007) which enables the conversion to electronic data upon completion of paper-based copies.

The first questionnaire is mailed out at study enrollment for completion before 24 weeks of gestation. Women are given reminder calls beginning at 20 weeks gestation or 3 weeks after the questionnaire is mailed, whichever is later, to answer participants' questions and encourage completion and return of the questionnaire.

The second questionnaire is mailed to all participants at 32 weeks gestation, to be completed between 34-36 weeks gestation. At 36 weeks gestation, women are contacted by telephone to provide a reminder about the questionnaire. A modified version of this questionnaire is used for women who delivered prior to receiving or completing the questionnaire.

The third questionnaire is designed for completion at four months post-partum. Women are contacted two weeks after their expected due date to determine the birthdate of their infant(s). The questionnaire is mailed to participants at 3.5 months postpartum.

### Obstetrical and Birth Record Data

The Alberta Perinatal Health (APH) database is an Alberta-based database that contains prenatal maternal and birth outcome information from all recorded births in the province. Study participants provide informed consent to access medical records. This enables the questionnaire data to be linked to their APH administrative data about birth outcomes, and to examine medical records to verify circumstances associated with preterm birth.

Due to the expected 18 month delay to populate and validate the APH database, study team members perform manual chart extractions for all preterm deliveries in the All Our Babies Cohort Study. This accelerates the collection of key medical record variables and is required to phenotype each preterm birth and enable case selection for the genetic analyses.

### Maternal Blood Specimens

Maternal blood samples are collected at 18-22 weeks gestation and at 28-32 weeks gestation either at a laboratory location or by a mobile phlebotomist. Participants are contacted at 17 and 27 weeks gestation by telephone and/or email to begin scheduling their first and second blood collections respectively. Collections can occur at any time of day and fasting is not required.

Four PAXgene™ blood RNA tubes (PreAnalytix/BD Canada, Mississauga, Ontario, Canada) are used at each blood collection. These tubes are specially designed to preserve RNA in whole blood at the time of collection. Blood is also collected into a heparin tube to isolate plasma (first collection), a serum collection tube (second collection) and into an EDTA tube for maternal DNA extraction.

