### Methods of Protecting Against Sources of Bias

All women who receive prenatal viral serology phlebotomy by Calgary Laboratory Service and consent to be contacted by researchers are contacted via telephone. Should they meet the inclusion criteria, the women are invited to participate in the All Our Babies Cohort Study. This recruitment strategy minimizes selection bias due to self-referral or patient populations at specific clinical practices and enables a citywide and surrounding area sampling approach.

Questionnaire data is collected prospectively, eliminating the influence of birth outcome on responses and potential for differential recall bias. However, the repeat use of standardized scales may introduce a form of bias where women remember answering the questions before and past answers influence responses on subsequent questionnaires. We anticipate that misclassification errors in exposure data will not be an issue in the information collected and generated from this cohort due to well-spaced and timely use of questionnaires.

Blood collections are offered at both a permanent laboratory location and by mobile phlebotomists to ensure that women are able to provide the blood sample at a location and time that is comfortable and convenient. The mobile phlebotomist option enables evening and weekend blood collections so that work hours are not a constraint. The flexibility of the blood collection options minimizes participant loss due to inconvenience or personal schedule demands.

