### Sample Size

Sample size calculations for the All Our Babies Cohort Study required complex considerations as maternal blood samples are destined for microarray analyses. Several power calculations for microarray methodologies exist, consequently sample size was determined and compared with two power calculation approaches. The first approach uses a two-class comparison model with a significance level of 0.001, a power of 0.95, one technical replicate per sample and estimated values of τ^2 ^+ 2 γ^2 ^= 0.25 and τ^2^/γ^2 ^= 4 (where τ^2 ^is the biological variance within class of log ratios and γ^2 ^is the technical variance of log ratios); the minimum sample size to identify a two-fold change in gene expression between classes is thus 25 patients in each study group [42,43]. An alternate approach is to consider the sample size required to detect a two-fold change in the expression levels of the 90% and 75% least-variable genes for a given set of false positive rates and power [42]; using previously published human tissue microarray data [43] and setting the false positive rates at 0.001 and a power of 0.9, this approach gave a minimum of 18 and 13 patients in each group to detect a two-fold change in expression levels for the 90% and 75% least-variable genes, respectively. Microarrays will be performed on RNA samples collected from 80 cases of spontaneous preterm birth and 80 matched controls (160 biological replicates) from samples collected at two time points (18-22 weeks and 28-32 weeks): a total of 320 microarrays. This sample size will allow prediction of:

1) idiopathic PTB (n~40), including

a) idiopathic PTB prior to 32 weeks gestation (n~13); and

b) idiopathic PTB between 32 and 37 weeks gestation (n~27);

2) PPROM and PTB (n~40), including

a) PPROM and PTB prior to 32 weeks gestation (n~13);

b) PPROM and PTB between 32 and 37 weeks gestation (n~27);

3) spontaneous PTB (n~80), including

a) spontaneous PTB prior to 32 weeks (n~25); and

b) spontaneous PTB between 32 and 37 weeks gestation (n~55).

Therefore, with a preterm birth rate of 9.1% in Alberta, an anticipated miscarriage rate of 5% and an anticipated loss to follow-up rate of 15% based on experience with other Alberta based cohorts [44], 2200 women will be enrolled in the All Our Babies Cohort Study. This should ensure 1800 women complete the study, of which approximately 180 will have preterm birth outcomes and approximately 120 of these will be spontaneous with or without PPROM.

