### Study Compliance

Strategies used to maintain participant involvement include reminder phone calls for outstanding questionnaires and providing incentives including public library gift certificates and grocery gift certificates for completed questionnaires. Mailing the questionnaires and providing postage paid envelopes has minimized time and costs to participants.

The All Our Babies Cohort Study participants are provided with two options for blood collections. Women may schedule an appointment through the research team at a central community laboratory clinic within Calgary. For participants unable or unwilling to travel to the laboratory clinic, the research team will send a certified mobile phlebotomist to the women's home or other neutral location of her choice for the blood collections. In appreciation for their time and commitment to the study, women are provided with department store gift certificates at the time of their blood collection.

Umbilical cord blood samples collected at the time of birth at local hospital births are sent to a single transfusion medicine laboratory location. The research team is notified of delivery and obtains these specimens after all clinical testing is completed. Women and their health care providers therefore do not need to do anything at the time of delivery for the study. Study team members need not be present at delivery units.

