### Proposed Type and Frequency of Analysis

#### Transcriptomic Analysis

RNA will be extracted from samples collected from identified cases (spontaneous preterm births with or without PPROM) and controls (term deliveries). Cases and controls will be 'loosely matched' such that each group has a similar distribution of maternal ages, prepregnancy body mass indexes and smoking status. Extracted RNA will be aliquoted into three tubes - one for Agilent RNA quality assessment, one for the transcriptomic microarray, and one for validation of microarray findings by real time polymerase chain reaction. Samples will be run on Affymetrix microarrays in two batches of 40 cases and 40 controls. All statistical analyses will be conducted on the full dataset generated from the microarrays.

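### Blood for RNA may be drawn at any hour, but the case-control matching list omits draw time; balancing and adjusting for it would be a cheap improvement

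*Protocol article*

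**What the plan says.** Protocol article, Maternal Blood Specimens, on the draws at 18-22 and 28-32 weeks: "Collections can occur at any time of day and fasting is not required". On the PAXgene tubes it adds: "These tubes are specially designed to preserve RNA in whole blood at the time of collection".

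Methods of Protecting Against Sources of Bias: "The mobile phlebotomist option enables evening and weekend blood collections so that work hours are not a constraint". That section presents the flexibility as a way to limit participant loss and does not discuss its effect on the assay. Study Compliance adds that, for women who cannot or do not wish to travel, "the research team will send a certified mobile phlebotomist to the women's home or other neutral location of her choice for the blood collections".

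Transcriptomic Analysis sets the matching of cases and controls loosely, so that "each group has a similar distribution of maternal ages, prepregnancy body mass indexes and smoking status". Draw time is not on that list, and Statistical Analysis does not name it.

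**The concern.** The measured quantity is blood RNA at the moment of the draw. The tube preserves what is present then, so it also preserves any difference due to clock time or a recent meal. The article gives no size for such differences. That they exist for some genes is an assumption here.

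Two consequences are possible:

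- **Noise.** If draw time is unrelated to outcome, it adds to within-class variance and lowers power.
- **Confounding.** If cases and controls differ systematically in draw time, genes that vary over the day differ between the groups without any link to preterm birth. A conceivable route runs through work hours, which the article ties to evening and weekend draws, and from there to socioeconomic status or stress. On these the Background says: "Other demographic factors such as low socioeconomic status [12] and maternal stress [13] have shown an association".

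The matching list is a stated rule that decides which 80 controls go on the arrays. A covariate can be added later if draw times exist, but the choice of controls cannot be redone cheaply once the arrays are run.

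**Working it through.** **Inputs from the article (Sample Size).** Variance term 0.25; per-gene significance level 0.001; two-fold change, that is 1 log2 unit; 80 cases and 80 controls; smallest subgroups about 13 cases.

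**Assumed inputs (not in the article).** Two-sided test; 0.25 taken as the within-class variance on the log2 scale (SD 0.5) without draw-time variation; average evening share 30%; evening-day difference D of 0.5 or 1.0 log2 units for a time-dependent gene.

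**The plan's own figure.** The article uses "a two-class comparison model with a significance level of 0.001, a power of 0.95, one technical replicate per sample" and concludes that "the minimum sample size to identify a two-fold change in gene expression between classes is thus 25 patients in each study group". The two-class formula 4(z₁₋α/₂ + z₁₋β)² × 0.25 / δ² with δ = 1 gives 4 × (3.291 + 1.645)² × 0.25 = 24.36, so 25. In this form 25 is the total of both classes. On the natural-log scale (δ = ln 2) the per-group formula 2(z₁₋α/₂ + z₁₋β)² × 0.25 / δ² gives 25.35, so 26 per group. The point made here does not depend on which reading applies.

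**Step 1: draw time unrelated to outcome.** With evening share p, the variance per class is v = 0.25 + p(1 − p)D². At p = 0.30:

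- D = 0.5: v = 0.25 + 0.21 × 0.25 = 0.3025 (+21%; SD 0.55)
- D = 1.0: v = 0.25 + 0.21 × 1 = 0.46 (+84%; SD 0.678)

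Power for a two-fold change comes from the noncentral t distribution with shift 1/√(2v/n):

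| Groups | v = 0.25 | v = 0.46 |
|---|---|---|
| 80 v 80 | > 0.999 | > 0.999 |
| 25 v 25 | > 0.99 | 0.95 |
| 13 v 13 | 0.89 | 0.52 |

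At 13 v 13 the shift falls from 5.10 to 3.76, against a critical value of 3.75. At D = 0.5 power there is 0.79. These rows assume equal groups. If 13 cases were compared with all 80 controls, the shift at v = 0.46 would be 1/√(0.46 × (1/13 + 1/80)) = 4.93 against 3.40, and power would be about 0.93.

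The test keeps its level. In 400,000 simulated comparisons per setting, with the same 30% evening share in both groups, the rejection rate stayed at about 0.001 for 80 v 80 and 13 v 13, at D = 0.5 and 1.0.

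**Step 2: draw time differs systematically.** With evening shares p₁ (cases) and p₀ (controls), the spurious difference is (p₁ − p₀)D and its standard error is √((v₁ + v₀)/80). Probability that p < 0.001 for a gene with no preterm-birth effect (noncentral t, 158 df):

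| Evening share | D | Spurious difference (log2) | Fold | P(p < 0.001) |
|---|---|---|---|---|
| 35% v 25% | 0.5 | 0.05 | 1.04 | 0.003 |
| 35% v 25% | 1.0 | 0.10 | 1.07 | 0.009 |
| 40% v 20% | 0.5 | 0.10 | 1.07 | 0.016 |
| 40% v 20% | 1.0 | 0.20 | 1.15 | 0.075 |

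Example, last row: v₁ = 0.25 + 0.24 = 0.49; v₀ = 0.25 + 0.16 = 0.41; SE = √(0.90/80) = 0.106; shift = 0.20/0.106 = 1.89; fold = 2^0.20 = 1.15.

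**The case against.** A reader might infer that a clock-time pattern is likely to be mistaken for a preterm-birth signature. The article does not support that. Draws are scheduled from 17 and 27 weeks in women whose outcome is not yet known. No section says that evening users have lower socioeconomic status or more stress, and employed women could as easily have higher status. Both the direction and the size of any gap are assumed. Chance imbalance does not fill the hole, because it is part of ordinary sampling variation and leaves the error rate at 0.001, as Step 1 shows. This objection stands, so confounding remains a possibility only.

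A reader might also infer harm to a comparison of early with late samples within women. Objectives and Proposed Outcome Measures state only comparisons of cases with controls at the two windows.

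Three further points limit the size:

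- Even the largest assumed case gives about 1.15-fold, against a two-fold design target, and D = 1.0 already assumes that clock time alone doubles expression.
- The 0.25 includes biological variance within class, so it may already contain some draw-time variation. Step 1 would then overstate the loss.
- Recording clock time and adjusting for it may sit in procedures or an analysis plan not shown. Silence in the article does not show that draw time goes unrecorded, and starting with univariate analysis does not rule out later adjustment.

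The flexible draw is deliberate and justified by retention. None of this changes the fact that the matching list is fixed in the article and leaves draw time out.

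**Conclusion.** The point holds as a modest improvement to a stated rule, not as a demonstrated bias. If draw time is independent of outcome, the cost is precision alone. That cost is negligible for two-fold changes at 80 v 80. It is material only in the subgroups of about 13 cases, where power falls from about 0.89 to about 0.52 with equal groups and an assumed 1.0 log2 evening-day difference, and by much less if all 80 controls are used. If a systematic gap of 10 to 20 points in evening share existed, time-dependent genes would be flagged at about 0.3% to 7.5% instead of 0.1%, with differences of at most about 1.15-fold. Evening shares and time-of-day effects are all assumed, because the article gives none. Priority: consider.

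**What to change.** Keep the flexible draw options. In Transcriptomic Analysis, add a time-of-day band at each collection window to the loose matching factors when the 80 controls are chosen. The pool is ample: about 1,800 completers less about 180 preterm births leaves roughly 1,620 term women. Include draw time, taken from the collection record, as a covariate in the case-control expression comparison at each window.

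The cost is slightly tighter control selection and one or two model degrees of freedom, with no additional visits or samples. The change is worth most before controls are selected and the 320 arrays are run.
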